**Aim 2: Trial feasibility and acceptability**		
**Objective**	**Method of assessment**	**Success criteria**
**Objective 2.1**: To measure the recruitment rates of participants (P)	• Recording number (*n*) of participants who were sent a participant information sheet, number who agreed to participate and number recruited per month	**Continue without modification** • Target of *n* = 35 participants recruited in 9 months (approx. 4/month) • Conversion rate of ≥ 30% (number sent PIS/ number who agreed to participate) **Stop** • Target of *n* = 35 participants recruited takes > 12 months (less than 3/month) • Conversion rate of ≤ 15% (number sent PIS/ number who agreed to participate)
**Objective 2.2**: To measure the completeness of data collection of performance-based and patient-reported outcome measures at baseline, 3- and 6-month post-baseline (P)	• Record number of PROMs returned to trial team and number of participants who completed performance-based outcomes during virtual outcome assessments at each timepoint	**Continue without modification** • ≤ 80% PROM and performance-based data collected at 3-month post-baseline • ≤ 70% PROM and performance-based data collected at 6-month post-baseline **Stop** • ≤ 50% PROM and performance-based data collected at 3-month post-baseline • ≤ 50% PROM and performance-based data collected at 6-month post-baseline
**Objective 2.3**: To determine the feasibility and acceptability of trial-related procedures (recruitment, outcome assessment) to participants and ROH research staff ((P)	• Participants: Semi-structured interviews • ROH research staff: Focus groups	**Continue with modification** • Thematic analysis identifies that trial participants and ROH research staff are satisfied (i.e. feasible and acceptable) with trial procedures (e.g. recruitment, outcome assessment) in semi-structured interviews and focus groups respectively **Stop** • Thematic analysis identifies that trial participants and ROH research staff are not satisfied (i.e. they do not perceive it is feasible and/or acceptable) with trial procedures (e.g. recruitment, outcome assessment) in semi-structured interviews and focus groups respectively

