**Objective 2.4**: To determine the feasibility and acceptability of utilising an accelerometer as the primary outcome in a definitive randomised controlled trial (S)	• % of accelerometers returned to research staff with valid data • Semi-structured interviews	• ≤ 70% of accelerometer data collected at 6-month post-baseline • Accelerometer data will be considered valid if it has been recorded for ≥ 10 h [42, 43] for ≥ 4/7 days, with at least one falling on a weekend [44–46] • Participants state that they believe that accelerometer is feasible and acceptable to use as the primary outcome measure in future definitive trial
**Objective 2.5**: To determine the acceptability of the patient-reported and performance-based outcome measures to participants ((S)	• Semi-structured interviews	• Participants report that they found the patient-reported and performance-based outcomes feasible and acceptable, and the time taken to complete was satisfactory for use in a definitive randomised controlled trial

Legend: *ISPACOT* Interpersonal support in physical activity consultations observational, *P* Primary feasibility outcome related to progression to definitive trial, *S* Secondary feasibility outcome

Once it has been established if each criterion has been met, further consultation with patient and public involvement (PPI) at Trial Steering Group meetings will be utilised to determine if and what modifications the intervention requires to progress to the full-scale RCT (e.g. adaptions to intervention to enable delivery in alternative NHS physiotherapy departments).

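### The three data-completeness thresholds in Table 3 (Objectives 2.2 and 2.4) carry a reversed inequality sign, so the progression rule is wrong as written

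*Protocol article*

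**What the plan says.** Table 3 of the protocol article lists the success criteria. Objective 2.2 is worded "To measure the completeness of data collection of performance-based and patient-reported outcome measures at baseline, 3- and 6-month post-baseline (P"; the letter P marks it, by the table legend, as a primary feasibility outcome bearing on progression to the definitive trial.

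- Continue without modification, 3 months: "≤ 80% PROM and performance-based data collected at 3-month post-baseline".
- Continue without modification, 6 months: "≤ 70% PROM and performance-based data collected at 6-month post-baseline".
- Stop, 3 months: "≤ 50% PROM and performance-based data collected at 3-month post-baseline".
- Stop, 6 months: "≤ 50% PROM and performance-based data collected at 6-month post-baseline".

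Objective 2.4, on the accelerometer as the future primary outcome, is marked secondary. Its numerical criterion is "≤ 70% of accelerometer data collected at 6-month post-baseline", with no continue label and no stop rule. It is assessed as the percentage "of accelerometers returned to research staff with valid data".

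The section on trial outcomes and success criteria says that overall success is to be judged against these pre-set criteria.

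**The concern.** Each percentage measures data obtained, so a high value is good. A continue criterion should therefore set a floor, but all three are printed as ceilings. For Objective 2.2 the ceilings at 80% and 70% also contain the whole stop region, which is at most 50%. The same poor result then meets two opposite decisions, while a very good result meets none.

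What is at stake is the use of a pre-specified rule. If the printed rule cannot be applied, someone must reinterpret it, perhaps once the completeness figures are known. That is what a priori criteria are meant to prevent. One of the three lines also concerns the measure intended as the primary outcome of the definitive trial.

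**Working it through.** **Inputs.** The thresholds are those of Table 3: 80% and 70% (Objective 2.2, continue), 50% (Objective 2.2, stop) and 70% (Objective 2.4). The denominator is n = 35, the target in the Sample size section. The plan gives no worked figure to reproduce for this rule.

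**Step 1: in percentages, for any n.** Let x be the percentage collected.
- If x ≤ 50, then x ≤ 70 and x ≤ 80 as well, so continue and stop hold together under Objective 2.2.
- If x > 80 at 3 months, or x > 70 at 6 months, neither holds.
- At x = 0 the continue rule is met; at x = 100 it is not.

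**Step 2: in counts.** 0.80 × 35 = 28; 0.70 × 35 = 24.5; 0.50 × 35 = 17.5. Each count c from 0 to 35 is classified by c/35, first as printed, then with ≥ in the continue and success lines only.

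| Criterion | Collected of 35 | Percentage | As printed | With ≥ |
|---|---|---|---|---|
| 2.2, 3 months | 0–17 | 0–48.6 | continue and stop | stop |
| | 18–27 | 51.4–77.1 | continue | intermediate |
| | 28 | 80.0 | continue | continue |
| | 29–35 | 82.9–100 | neither | continue |
| 2.2, 6 months | 0–17 | 0–48.6 | continue and stop | stop |
| | 18–24 | 51.4–68.6 | continue | intermediate |
| | 25–35 | 71.4–100 | neither | continue |
| 2.4, 6 months | 0–24 | 0–68.6 | success | not met |
| | 25–35 | 71.4–100 | not met | success |

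**Step 3: how much of the range is affected (Objective 2.2).** There are 36 possible counts.
- 3 months: 18 are contradictory (0–17), 10 + 7 = 17 fall in the wrong class (18–27 and 29–35), and 1 is right (28).
- 6 months: 18 are contradictory (0–17), 7 + 11 = 18 fall in the wrong class (18–24 and 25–35), and none is right.

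**Step 4: could the sign be meant, or be a reading fault?**
- If the figures were percentages missing, ≤ would make sense for continuing. But the lines speak of data collected, and a stop rule at 50% or less makes sense only for data collected.
- Objective 2.1, in the same table, has the expected pattern: continue at ≥ 30% conversion, stop at ≤ 15%.
- The sign ≥ prints correctly elsewhere in the table (≥ 50% and ≥ 4/7 in Objective 1.3; ≥ 10 h in Objective 2.4 itself), so a PDF-reading fault is unlikely.
- No other section restates these thresholds with the opposite sign.

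**The case against.** The best defence is that the intent is plain. Objective 2.1 shows the direction, the 50% stop rule confirms it, and the results go to Trial Steering Group meetings with patient and public involvement. Such a group is unlikely to treat complete data as a shortfall. This stands, and it limits the likely practical harm. It does not make the printed rule usable, and the article offers no other statement of it.

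Several stronger readings are tempting, and the document does not support them.

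- *The continue/stop clash affects both objectives.* It exists only in Objective 2.2. Objective 2.4 has no stop rule, so its fault is direction alone.
- *Complete data would stop the trial.* It would not: 35/35 misses the continue or success criterion but does not meet stop.
- *The rule gives the wrong decision over most of its range.* At n = 35 about half the counts are contradictory and about half misclassified.
- *The numerator is also faulty.* A reader might infer this because the Objective 2.2 method includes "Record number of PROMs returned to trial team", while the quantitative analysis section excludes partially completed PROMs. But that section also reports partial and non-completion as percentages at each timepoint, and the criterion itself speaks of data collected.
- *The accelerometer denominator is returned devices only.* The wording of Objective 2.4 can be read that way, but it reads as naturally as the share of devices that came back with valid data. A condensed article may leave the exact denominator to the full protocol.

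**Conclusion.** Wrong as written. All three completeness thresholds have the inequality reversed; two of them belong to a primary progression outcome. As printed, Objective 2.2 reaches the evidently intended class without contradiction for one of 36 possible counts at 3 months and for none at 6 months. Objective 2.4 is inverted throughout.

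The counts assume that all 35 participants are recruited and form the denominator, and that PROM and performance-based data are treated as one count. The contradiction in percentages needs neither assumption. The conclusion about intent rests on the word collected, the 50% stop lines and the pattern of Objective 2.1.

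**What to change.** In Table 3, change ≤ to ≥ in three places: the 3-month continue line of Objective 2.2 (to ≥ 80%), its 6-month continue line (to ≥ 70%), and the accelerometer line of Objective 2.4 (to ≥ 70%). Keep both Objective 2.2 stop lines at ≤ 50%.

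At n = 35 the classes no longer overlap: continue 28–35, intermediate 18–27 and stop 0–17 at 3 months; continue 25–35, intermediate 18–24 and stop 0–17 at 6 months; accelerometer success 25–35.

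The cost is three characters. Sample size, data collection and analysis do not change. The correction is best recorded and dated before anyone compares completeness results with the table.

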#### Trial outcomes and success criteria

Once data analyses are complete, the overall trial’s success (i.e. trial-related procedures and intervention feasibility and acceptability) will be determined by evaluating the results against a priori established criteria for success (Table 3). The criteria were established by the Trial Management Group, which includes experts in musculoskeletal physiotherapy, ROH physiotherapists and researchers with expertise in trial methodology and behaviour change supported by contemporary literature in contemporary feasibility trial methodology [37]. Each criterion will be evaluated against guidance outlined by Thabane et al. (2010) [38] to determine if progression to a definitive trial is recommended. Possible outcomes include the following:Stop: A definitive trial is not feasible.Continue with modification: Modification of the protocol is required to make definitive trial feasible.Continue without modification: Modification of the protocol is not required to make definitive trial feasible but requires close monitoring.Continue without modifications: A definitive trial appears feasible.

**Table 3 Tab3:** Trial outcomes and success criteria

Aim 1: Intervention feasibility and acceptability		
**Objective**	**Method of assessment**	**Success criteria**
**Objective 1.1:** To determine the feasibility and acceptability of the complex and multicomponent behaviour change intervention to participants and treating physiotherapists (P)	• Participants: Semi-structured interviews •Physiotherapists: Focus group	**Continue without modifications**: Thematic analysis identifies that trial participants and treating physiotherapists found the intervention satisfactory (i.e. it was feasible and acceptable) in semi-structured interviews and focus groups respectively **Stop**: Thematic analysis suggests that trial participants and treating physiotherapists did not find the intervention satisfactory (i.e. it was unfeasible and/or unacceptable)

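### Table 3 labels the favourable result of primary Objective 2.3 as needing protocol modification, so no result on that criterion reaches a without-modification category

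*Protocol article*

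**What the plan says.** The section on trial outcomes and success criteria says that results will be judged against criteria set in advance in Table 3, and it lists four possible outcomes:

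- Stop.
- The second outcome, given as "Continue with modification: Modification of the protocol is required to make definitive trial feasible".
- *Continue without modification*, defined as "Modification of the protocol is not required to make definitive trial feasible but requires close monitoring".
- *Continue without modifications*, for a definitive trial that appears feasible.

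Table 3 then attaches conditions to these outcomes for each objective. Objective 2.3 concerns recruitment and outcome-assessment procedures, as seen by participants (interviews) and by hospital research staff (focus groups). It is marked (P), which the table legend explains as "Primary feasibility outcome related to progression to definitive trial".

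Objective 2.3 has two categories. Under "Continue with modification" the condition is: "Thematic analysis identifies that trial participants and ROH research staff are satisfied (i.e. feasible and acceptable) with trial procedures". Under Stop the condition begins: "Thematic analysis identifies that trial participants and ROH research staff are not satisfied (i.e. they do not perceive it is feasible and/or acceptable". No third category is given.

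For comparison, Objective 1.1 is also primary and also judged from interviews and a focus group. It places the condition "Thematic analysis identifies that trial participants and treating physiotherapists found the intervention satisfactory" under *Continue without modifications*.

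**The concern.** The label and the condition under it contradict each other. The condition says that the procedures were found feasible and acceptable. The label, by the article's own definition, says that the protocol must be changed before a definitive trial can be feasible.

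Trial procedures are the subject of one of the trial's two primary aims, and the criteria are fixed in advance so that they are not reinterpreted once the data are in. With this label the team has two poor options if participants and staff are satisfied. Following the text means reporting that the procedures need modification when the evidence says they do not. Reading *with* as *without* means choosing the category for a primary criterion after the results are known.

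**Working it through.** No arithmetic is involved beyond counting labels. The check sets the favourable label of each primary objective in Table 3 beside the outcome definitions in the text above the table.

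| Primary objective | Subject | Label on favourable result | Other category |
|---|---|---|---|
| 1.1 | Intervention feasible and acceptable | Continue without modifications | Stop |
| 1.2 | Training acceptable | Continue without modifications | Stop |
| 2.1 | Recruitment | Continue without modification | Stop |
| 2.2 | Data completeness | Continue without modification | Stop |
| 2.3 | Trial procedures feasible and acceptable | Continue with modification | Stop |

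**Step 1: the label on 2.3.** Four of the five primary objectives put a without-modification label on their favourable result, and one (2.3) does not. Objective 2.3 has only two categories and neither is a without-modification category. Every result to which the table assigns a category therefore leads to modification or to stopping.

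**Step 2: the closest comparator.** Objectives 1.1 and 2.3 use the same kind of evidence (thematic analysis of interviews and focus groups) and the same gloss on satisfaction (feasible and acceptable). They carry opposite labels, and nothing in the article gives a reason for the difference.

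**Step 3: whether other text repairs it.** The list of four outcomes is general. It names the without-modification outcomes, but Table 3 attaches no condition to them for 2.3. The paragraph after Table 3 provides for consultation with patient and public representatives at steering-group meetings. That takes place after each criterion has been judged, and it concerns changes to the intervention, not to trial procedures. Neither passage supplies the missing category.

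**Step 4: the two similar outcome names.** The third and fourth outcomes differ in name only by the plural s, although their definitions differ (close monitoring needed, or trial appears feasible). Table 3 uses the plural in 1.1 and 1.2 and the singular in 2.1 and 2.2.

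- Read literally, a favourable result on 2.1 or 2.2 reaches only the close-monitoring outcome. Then 2 of 5 primary objectives can reach the top outcome (1.1 and 1.2), and 3 of 5 cannot (2.1, 2.2 and 2.3).
- If the two forms are meant to be the same, 4 of 5 can reach it and only 2.3 cannot.

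The article does not say which reading applies. The result for 2.3 is the same under both.

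**The case against.** The strongest reply is that this is a one-word slip with an obvious intent. The condition is spelled out as feasible and acceptable, the only alternative is Stop, and all four other primary objectives follow the expected pattern. A trial management group is unlikely to read it as obliging a protocol change. The practical effect is also limited: the trial is single-arm with descriptive analysis, the label changes no data collection or estimate, and it would not wrongly stop the programme, since both labels mean continuing.

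Much of this stands. A slip is the likeliest explanation, and the consequence is a misclassified criterion, with no harm to participants or to the data. It does not remove the point. The article does not say that the label is a slip, and a progression criterion set in advance should not depend on readers correcting it after the results are in. Nor is this a detail left to a fuller document: the printed criterion states the wrong thing.

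A reader might go further and infer that the trial as a whole could never return a verdict of feasible without modification. The article does not support that. It says that each criterion will be evaluated, and it calls the primary criteria related to progression, but it does not say that the least favourable category among them sets the overall verdict. The inference needs that rule, and the rule is not written.

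A reader might also want a middle category for mixed satisfaction. That is a separate design preference. Objectives 1.1 and 1.2 have only two levels as well, and the error in 2.3 can be corrected without adding a third.

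**Conclusion.** The point holds at the level of Objective 2.3 and needs no assumption there. As printed, the most favourable result on this primary criterion falls in a category defined as requiring protocol modification, and no result on it can reach a without-modification category. This contradicts the condition's own wording and the labelling of the other four primary objectives.

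The size of the effect on the overall progression decision cannot be stated, because there is no written rule for combining criteria. The near-identical outcome names are a secondary ambiguity: how many primary objectives can reach the top outcome depends on whether the singular and plural forms are meant to differ.

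**What to change.** In Table 3, relabel the satisfied result of Objective 2.3 *Continue without modifications*, in line with Objective 1.1. Make the change, and record it, before the interview and focus-group findings are set against the criteria.

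As a secondary edit, give the third outcome a distinct name, for example *Continue with close monitoring*. Then go through Table 3 so that each label is unmistakably one of the four outcomes, and state for 2.1 and 2.2 which of the two without-modification outcomes is meant.

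Both changes affect wording only. They need no change to data collection, sample size or analysis.

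### No primary progression criterion in Table 3 measures the yield of valid accelerometer data, the planned primary outcome of the definitive trial, and the one threshold for it is printed with its sign reversed

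*Protocol article*

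**What the plan says.** All references are to the protocol article.

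- **Role of the accelerometer.** Table 3, Objective 2.4, concerns "utilising an accelerometer as the primary outcome in a definitive randomised controlled trial (S". Table 4, headed as the secondary outcomes planned for the randomised trial, does not list the accelerometer. The Trial design section gives 6 months as that trial's planned primary end point.
- **Meaning of the labels.** The Table 3 legend defines P as "Primary feasibility outcome related to progression to definitive trial" and S only as "Secondary feasibility outcome".
- **Criterion for Objective 2.4.** It has a yield threshold, "≤ 70% of accelerometer data collected at 6-month post-baseline", a validity rule beginning "Accelerometer data will be considered valid if it has been recorded for ≥ 10 h" (on at least 4 of 7 days, one of them at a weekend), and an interview criterion. None carries a Continue, Modify or Stop label.
- **Primary completeness criterion.** Objective 2.2 is "To measure the completeness of data collection of performance-based and patient-reported outcome measures at baseline, 3- and 6-month post-baseline (P". Its method of assessment is the "number of PROMs returned to trial team and number of participants who completed performance-based outcomes". One of its Stop levels is "≤ 50% PROM and performance-based data collected at 6-month post-baseline".
- **Use of the criteria.** The section Trial outcomes and success criteria says that each criterion is evaluated to decide whether to recommend progression. Stop and continuing with modification are among the possible results. It gives no rule for a failed S criterion.

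**The concern.** The labels do not match the outcome hierarchy of the trial being prepared. Incomplete data on the definitive trial's secondary outcomes can trigger a Stop. Incomplete data on its primary outcome have no stated consequence.

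The two can come apart in practice. Accelerometers are posted out, fitted by the participant and posted back, and a record counts only if the wear-time rule is met. The Quantitative data analysis section also excludes partial accelerometer data. A participant can attend the virtual assessment and return the questionnaires, so counting towards Objective 2.2, yet give no valid accelerometer record.

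At stake is a recommendation to proceed, formally supported by every P criterion, to a trial whose primary outcome would be missing for a large share of participants. The reversed sign adds to this, because read literally it turns a poor yield into a success.

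**Working it through.** **1. Which criteria count accelerometer data?**

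| Objective | Label | Stop level? | Counts valid accelerometer data? |
|---|---|---|---|
| 1.1 Intervention | P | yes, qualitative | no |
| 1.2 Training | P | yes, qualitative | no |
| 1.3 Fidelity | S | no | no |
| 2.1 Recruitment | P | yes, numeric | no |
| 2.2 Completeness | P | yes, numeric | no |
| 2.3 Trial procedures | P | yes, qualitative | no (satisfaction only) |
| 2.4 Accelerometer | S | no | yes |
| 2.5 Outcome measures | S | no | no |

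There are five P criteria, each with a Stop level, and none counts accelerometer data. Objective 2.2 cannot be read to include the device, because the data collection section names accelerometer, patient-reported and performance-based outcomes as three separate things.

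**2. The printed threshold, taken literally.** Take n = 35 (the target in the Sample size section), all in the denominator. Then 0.70 × 35 = 24.5, so the printed criterion is met by 0 to 24 valid records and failed by 25 or more (25/35 = 71.4%). With X ~ Binomial(35, p), the probability of meeting it as printed is P(X ≤ 24):

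- p = 0.50: 0.99
- p = 0.80: 0.08

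The sign must be an error. The Continue levels of Objective 2.2 (80% and 70%) carry the same sign, and their ranges then contain that objective's own Stop range of 50% or less.

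**3. Graded levels at 70% and 50%.** Continue needs X ≥ 25. The lower level is X ≤ 17, since 0.50 × 35 = 17.5. The document gives no expected rate of valid return, so the true rates below are assumptions spanning a range.

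| True valid-return rate | P(X ≤ 17) | P(X ≥ 25) |
|---|---|---|
| 30% | 0.99 | < 0.001 |
| 40% | 0.89 | < 0.001 |
| 50% | 0.50 | 0.008 |
| 60% | 0.11 | 0.11 |
| 70% | 0.006 | 0.51 |
| 80% | < 0.001 | 0.93 |

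Under the present table, low yield alone triggers no Stop at any of these rates.

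**4. Precision.** Wilson 95% interval: centre (p̂ + z²/2n)/(1 + z²/n), half-width z√(p̂(1−p̂)/n + z²/4n²)/(1 + z²/n), with z = 1.96 and n = 35, so z²/n = 0.110.

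- 25/35: p̂ = 0.714, centre 0.693, half-width 0.144, giving 55% to 84%.
- 17/35: p̂ = 0.486, centre 0.487, half-width 0.157, giving 33% to 64%.

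The intervals overlap, so n = 35 does not separate the two levels sharply. The same holds for Objective 2.2, where the protocol accepts graded levels at this sample size.

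**The case against.** A reader might infer that the plan ignores accelerometer completeness, or that it cannot answer whether the definitive trial is feasible. The document does not support either reading:

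- Every criterion is to be evaluated, not only those marked P. Objective 2.4 has a yield threshold, a validity rule and an interview criterion, so the yield will be measured and judged.
- Objective 2.3 is P, has a Stop level and covers outcome assessment, which includes the accelerometer. A device that participants or research staff find unacceptable could therefore stop progression.
- Stop means that a definitive trial is not feasible. A poor yield need not mean that, since the accelerometer procedures or the primary outcome could be changed. A self-report activity questionnaire is already collected at all three time points.
- No S objective has a Stop level, so the table is internally consistent.
- Devices and questionnaires are posted together and share a return envelope and a 2-week reminder. Near-zero yield alongside good questionnaire return is thus a logical extreme, not a forecast.

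Much of this stands, and it limits the point. It does not remove it. Objective 2.3 rests on satisfaction, judged from interviews with 8 to 10 purposively chosen participants and a staff focus group, and cannot measure a valid-data rate. Worn-but-invalid records are plausible even when devices come back. The later Steering Group consultation is described as settling modifications to the intervention, not the choice of outcome. And evaluating every criterion does not say what a failed Objective 2.4 does. The absence of a Stop level also matters more here than in Objectives 1.3 and 2.5, because only Objective 2.4 tests the future primary outcome.

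**Conclusion.** The point holds in a bounded form. What lies outside the P criteria is the quantitative yield of valid 6-month accelerometer data. All five P criteria can be met while that yield is low, and no consequence is stated. The one threshold that addresses it is printed in the wrong direction. The data will be collected and reported either way, so the defect is in the decision rule and not in the evidence.

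This rests on the Table 3 labels and legend as printed. It also reads Objective 2.2 in its evident sense, with its Continue levels as minimums. The probabilities are illustrative: they assume full recruitment to 35, all 35 in the denominator, independent participants, and true rates that the document does not give.

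**What to change.** In Table 3, mark Objective 2.4 as P and replace the threshold. This openly reverses the printed sign.

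- **Continue without modification:** at least 70% of enrolled participants give valid 6-month accelerometer data under the existing wear-time rule (25 or more of 35).
- **Continue only with modification of the accelerometer procedures:** below 70% but above 50% (18 to 24 of 35).
- **At 50% or less (17 or fewer of 35):** do not proceed to a randomised trial with the accelerometer as primary outcome unless the primary outcome is changed.

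The 50% level is borrowed from Objective 2.2. Whether a tolerance set for secondary outcomes suits a primary one is a judgement for the Trial Management Group. The lowest level is worded as a bar on this primary outcome and not as a full Stop, because low yield can be met by changing the outcome. Enrolled participants are the denominator so that devices never returned count as missing. The Continue levels of Objective 2.2 need the same sign correction in the same edit.

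The cost is wording only, with no new data. The progression rule becomes slightly harder to pass. At a true rate of exactly 70% the Continue level is reached only about half the time (0.51), so a result near a boundary should be reported with its confidence interval.
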